**Protocol Attachment LYDZ(b).2.**

**Clinical Laboratory Tests**

**Clinical Laboratory Tests**

**Hematologya,b**: **Clinical Chemistrya,b** Hemoglobin **Serum Concentrations of**: Hematocrit Sodium

Erythrocyte count (RBC) Potassium Mean cell volume (MCV) Bicarbonate Leukocytes (WBC) Chloride Neutrophils, segmented Total bilirubin

Neutrophils, juvenile (bands) Alkaline phosphatase

Lymphocytes Gamma-glutamyl transferase (GGT) Monocytes Alanine aminotransaminase (ALT/SGPT) Eosinophils Aspartate aminotransaminase (AST/SGOT) Basophils Blood urea nitrogen (BUN)

Platelets Serum creatinine

Cell morphology Uric acid

Phosphorus

**Urinalysisa,b**: Calcium

Specific gravity Glucose (random) Protein Total protein Glucose Albumin

Blood Cholesterol

Nitrate Creatine kinase (CK) Urine leukocyte esterase

Microscopic examination of sediment **CKMBa,b**

**Serum Cotininea,b**

**Urine Drug Screen a,b,d Serum Pregnancy Test** (females of child- bearing potential only)**a,b,c**

**CYP2D6 enzyme functio**n – whole blood sample**a,f**

**Whole Blood Alcohol a,b,e**

**TSH a,b**

Abbreviations: CYP2D6 = cytochrome P450 2D6; a genetic test for determining CYP2D6 enzyme function (extensive and poor metabolizers).

a Assayed by Lilly-designated Lab.

b Results will be validated by the Central Lab at the time of initial testing. CYP2D6 results will be validated by Lilly during analyses of the data at the end of the study.

c For females of child-bearing potential, a pregnancy test is required at Visit 1 and may be performed at any

other time at the investigator's discretion.

d A urine drug screen is required at Visit 1 and may be performed at any other visit at the investigator's discretion.

e Alcohol testing is required at Visit 1 and may be performed at any other visit at the investigator's

discretion.

f A blood sample may be drawn assayed for cytochrome P450 2D6 (CYP2D6) genotype per investigator request in the event of a clinically significant overdose, serious adverse event (SAE), or if a patient is found to have a new onset of neurological signs and symptom. The Lilly Study Physician must be contacted for approval to draw and analyze the sample.

**Protocol Attachment LYDZ(b).3.**

**Concomitant Medication List**

**Prescription and Over-the-Counter Excluded Drugs (N) and Drugs Allowed (Y) as**

**Concomitant Medications, Study Period I, II, III**

Prescribed and Over-the Counter Drug or Drug Class Episodic Use (as needed) Chronic Use Acetaminophene Ye Ye Allopurinol Y Y Amantadine N N Amiodarone N N Analgesics **f** (non narcotic and except acetaminophen) Yf Yg Anorexics N N Antacids Y N

Anti-inflammatory drugs (nonsteroidal) Y Y Antiasthma agents (except steroids)**a** Y Y Antibiotics (except chloramphenicol) Y Y Anticoagulants N N Anticonvulsants N N Antidepressants N N Antipsychotics N N Antidiarrheal preparations Y N Antiemetics Y N Antihistamines (except diphenhydramine)b Y Y Antihypertensivesc Y Y Benzodiazepines N N Beta-Blockers**h** N Y**h** Calcium Channel blockers Y Y Celecoxib N N Chlorpheniramine N N Cimetidine N N Cough/cold preparations (nonsympathomimetic)**a** Y N Cromolyn sodium Y Y Diphenhydramine Y N Diuretics Y Y Doxorubicin N N

Eszopiclone N N

H2 Blockers (except nizatidine and ranitidine are N N

permitted

Halofantrine N N Haloperidol N N

Health-food supplements that, in the investigator’s N N

opinion, may have central nervous system activity (e.g. St. John’s Wort, melatonin)

Hormones Y Y Indinavir N N Insulin Y Y Laxatives Y Y Lithium N N Narcotics **f** Y N Oral hypoglycemic agents Y Y Oral contraceptives Y Y Table (continues)

**Prescription and Over-the-Counter Excluded Drugs (N) and Drugs Allowed (Y) as**

**Concomitant Medications, Study Period I, II, and III**

| Other psychotropic drugs | N | N |
| --- | --- | --- |
| Psychostimulants | N | N |
| Quinidine | N | N |
| Ranitidine | Y | Y |
| Ritonavir | N | N |
| Ramelteon | N | N |
| Sedative hypnotics  Steroids (oral or inhaled) | N Y**d** | N N |
| Terbinafine | N | N |
| Tryptophan  Zaleplon | N N | N N |
| Zolpidem | N | N |

a Medications may not be used on a daily basis if they are primarily sympathomimetic, e.g., albuterol.

b Antihistamines are not to be used for sedation.

c Clonidine, guanabenz, guanfacine, methyldopa, reserpine, guanethidine, guanadrel, metyrosine, and ketanserin should not be used.

d Short term oral or inhaled steroids are permissible in certain instances including significant allergic

reactions or acute asthma reactions. Please consult the Lilly physician or Lilly designee.

e Use of acetaminophen is limited to 2 grams per day.

f Acute use analgesics and narcotics are allowed if used to treat acute injury or surgical procedure for no longer than 3 days. Narcotics are not allowed during the screening period (before Visit 2).

g Up to 325 mg /day of aspirin is permitted for cardiac prophylaxis.

h Patients may use beta-blockers for treatment of hypertension, but not for treatment of anxiety.

**Prescription and Over-the-Counter (OTC) Medications Prohibited as Concomitant Medications in Protocol B4Z-US-LYDZ(b).**

Use of all concomitant medication (prescription and OTC) must be recorded.

• Concomitant use of monoamine oxidase inhibitors (MAOIs) is never allowed while subjects are taking atomoxetine.

• Atomoxetine is metabolized primarily by cytochrome P450 2D6 (CYP2D6). Many other drugs are metabolized by CYP2D6. Thus, there is the possibility that atomoxetine could alter the metabolism of other

CYP2D6 substrates. Although no such interactions have been observed in

clinical pharmacology studies, when given in combination, plasma concentrations of these drugs and/or concentrations of atomoxetine could be altered. Thus, drugs that are metabolized by CYP2D6 should be used with caution, and the Lilly physician responsible for monitoring the trial should be consulted before such drugs are used in conjunction with atomoxetine. Such drugs include, but are not limited to:

| **SUBSTRATES OF CYP2D6** | |
| --- | --- |
| **CLASS** | **SUBSTRATES** |
| Neuroleptics | perfenazine, thioridazine |
| Antiarrythmic agents | encainide, flecainide, mexiletine, propafenone, sparteine |
| Beta-blockers | Metoprool, propanol, timolol |
| Opioids | codeine, dextromethorphan, hydrocodone, tramadol |
| Others | debrisoquine, perhexiline, phenformin |

Atomoxetine is metabolized primarily by cytochrome P450 2D6 (CYP2D6), and concomitant use of drugs that inhibit this enzyme could result in increased plasma concentrations of atomoxetine. Concomitant administration of atomoxetine and CYP2D6 inhibitors is not permitted in this study. Such drugs include, but are not limited to:

| **INHIBITORS OF CYP2D6** | |
| --- | --- |
| **CLASS** | **INHIBITORS** |
| Antidepressants | clomipramine, fluoxetine, moclobemide, paroxetine |
| Neuroleptics | haloperidol |
| Antiarrythmic agents | amiodarone, quinidine |
| Antiinfectives | halofantrine, ritonavir, terbinafine |
| Others | celecoxib, chlorpheniramine, cimetidine |

More complete lists of CYP2D6 inhibitors and substrates may be found on the internet

[(http://m](http://medicine.iupui.edu/flockhart/))e[dicine.iupui.edu/flockhart/).](http://medicine.iupui.edu/flockhart/)) If in doubt, please contact Lilly.

**Protocol Attachment LYDZ(b).4.**

**Adult Electrocardiogram Exclusion Criteria**

**Eli Lilly and Company**

**Electrocardiogram Exclusion Criteria**

at baseline during study ( if not present at

baseline)

absolute

consult sponsor prior to

discontinue study drug and consult

consult

**ECG Finding** exclusion admission sponsor sponsor

**Rate and Intervals**

Heart Rate ≤40 bpm √ √ Heart Rate ≥130 bpm √ √ QTcBazett’s interval >500 msec √ √

Change from baseline of QTc > 60msec n/a n/a √

**Rhythm**

Junctional Rhythm (JUNCT-R) √ √ Junctional Bradycardia (JUNBRAD) √ √ Junctional Tachycardia (J-TACH) √ √ Undetermined Rhythm (UR) √ √ Atrial Flutter (AFL) √ √ Atrial Fibrilation (AFIB) √ √ Supraventricular Tachycardia (SVT) √ √ Multifocal Atrial Tachycardia (MULT-AT) √ √

Chaotic Atrial Mechanism (CAM) √ √

Unusual P Axis, Possible Ectopic Atrial Rhythms √ √

(EAR)

Bigeminy (BIGEM) √ √

Trigeminy (TRIGEM) √ √

Ventricular Tachycardia or Supraventricular with √ √

Aberration (VTACH)

Wide QRS Tachycardia (WQTACH) √ √ Torsades de Pointes (TOR) √ √ Ventricular Flutter (VFL) √ √ Ventricular Fibrillation (VFIB) √ √ Accelerated Idioventricular Rhythm (AIVR) √ √ With Failure to Capture Consistently (FAILCAPT) √ √

With Failure to Sense Patient’s Own Activity √ √

(FAILSENS)

**Eli Lilly and Company**

**Electrocardiogram Exclusion Criteria (concluded)**

at baseline during study ( if not present

at baseline)

absolute

consult sponsor prior to

discontinue study drug and consult

consult

**ECG Finding** exclusion admission sponsor sponsor

**Conduction**

Sinus Arrest or Block (SAB) √ √

2nd Degree A-V Block (MBZI) √ √

2nd Degree A-V Block (MBZII) √ √ Complete Heart Block (CHB) √ √ AV Dissociation (AVDIS) √ √

**Myocardial Ischemia/Injury/Infarction**

Hyperacute T Wave Abnormality (HYPERT) √ √

ST Depression Consider Ischemia (STDPIN) √ √

Injury Pattern (INJ) √ √

Marked ST Depression, Consider Subendocardial √ √

Injury (SBINJ)

ACUTE MI (ACUMI) √ √

**T Waves**

Tracing Suggests Hypercalcemia (HIGHCA) √ √ Tracing Suggests Hypocalcemia (LOWCA) √ √ Tracing Suggests Hypokalemia (LOWK) √ √ Tracing Suggests Hyperkalemia (HIGHK) √ √

**Additional Findings**

PR Segment Depression, Consider Pericarditis (PRD) √ √

Acute Pericarditis (PCARD) √ √

**Protocol Attachment LYDZ(b).5.**

**Community Sample**

**Introduction and Rationale**

There is a need to better understand the issues of the ADHD complex patient – those with psychiatric co-morbidities. However, to homogenize comparison groups in research clinical trials to facilitate analysis, the complex patients are routinely excluded from clinical trials. As a result, there is a gap between the “real world” clinical patient who may have a complicated clinical presentation and the “simpler patient” that is studied in clinical trials (Rothwell. 2005). The Agency for Healthcare Research and Quality (AHRQ) identified this gap, stating “Studies are also needed to determine whether comorbid factors (for example, anxiety and depressive disorders) influence response to treatment.” (Jadad AR et al. 1999). There have been large epidemiological studies done

to document the extent to which these comorbidities with ADHD exist (Kessler et al.

2006), but little to examine the course of the disorder as a function of these comorbidities.

The community sample (CS) is a superset of subjects who do not qualify or qualify but choose not to participate in the randomized research clinical trial (RCT). Non- interventional health outcomes data via web-based self reporting will be collected via a study website from the CS participants on the same schedule as the RCT participants. For comparative purposes within the community sample, some “trial-like” patients, or patients that are from a screening perspective similar to those who enrolled in the RCT will be recruited. These trial-like patients will be recruited through a central advertising system in cities where a clinical research study site is not available. The participants of

the CS will interface only with the study website and will be independent of the RCT and investigator trial sites. Results from the community sample will be reported separately from the main protocol study report.

**Objectives and the Corresponding Measures**

The primary objective of this CS is to compare the clinical course of ADHD in trial-like and clinically complex patients in a community sample. The “trial-like” group will comprise of respondents who pass the web inclusion/exclusion screen: indicate a willingness to participate in an RCT but do not have a site in their geographic region or declined to participate though a site was available in their region. The “complex” group is defined as subjects who screened positive on the ASRS screener for likelihood of meeting ADHD criteria but who did not otherwise meet the web-based inclusion/exclusion screener for the RCT. The null hypothesis for the CS is: “ADHD patients in the clinically complex group show similar changes over time in ADHD symptom severity as measured by the CAARS-S:SV total ADHD symptom score as compared to patients not in the clinically complex group.”

Secondary objectives include:

• Expansion of prior work regarding treatment selection preferences in typical practice. This would include an assessment of the baseline severity of psychiatric

comorbidities using scores from self report scales (see study schedule of events, Session 1).

• Compare ADHD symptom severity and improvement as measured by the CAARS-S:SV between patient groups with and without presumed comorbidities (for example, anxiety and depression) as measured by self-report of diagnosis, and available scales.

• Compare ADHD symptom severity and improvement as measured by the CAARS-S:SV between patient groups formed by treatment selection (for example, atomoxetine v. alternative).

Secondary objectives are dependent upon sufficient numbers of patients with various comorbidities and treatments enrolling in the CS. There will be no assignment to treatment in this community sample, so it is possible there will be an inadequate sample to address all of these objectives. The sampling frame for the CS is designed around the clinical presentation of the patients, as “trial-like” and “complex”.

**Study Design and Brief Discussion of the Design**

This is a prospective, longitudinal, non-interventional community sample which is comprised of a superset of subjects who do not qualify or qualify but choose not to participate in the randomized research clinical trial (RCT). Subjects eligible for the CS are those who: completed initial web screening for the study, screened positive for the ASRS criteria for ADHD by obtaining a score of 14 or greater on the ASRS v1.1, raw scoring method, but did  **not** qualify for the RCT for any of the following reasons:

• did not meet full inclusion/exclusion for the RCT;

• met full inclusion/exclusion criteria but no site located within their geography; or

• met full inclusion/exclusion criteria and is eligible for RCT but does not wish to participate in the RCT.

Other than the criteria stated above, there are no exclusionary conditions for the CS.1For subjects eligible for the CS and who are interested in participating, the informed consent for the community sample will be obtained via the website prior to collecting any information. Non-interventional health outcomes data via web-based self reporting will be collected via a study website from the CS participants on the same schedule as the RCT participants. A separate schedule of events for the CS is provided in this attachment. Subjects participating in the CS will interface only with a study website and will not be seen by an investigator or clinical trial site. Some additional information on health resource utilization (for example, trips to the emergency room, treatments obtained) will be collected from the CS.

1 While this openness may result in the inclusion of patients with suicidal ideation or terminal illness, such patients exist in clinical practice and excluding them would be counter to the goal of characterizing real-life complexities. Consent forms will clearly indicate that no live or real-time review of forms will occur, nor will health care services be provided. Care will be taken, however, to provide referral information in the event that structured survey responses (there will be no opportunity for free-text responses) suggest increased risk of self-harm. For example, if a patient endorses the PHQ-9 item, indicating “Thoughts that

you would be better of dead or hurting yourself in some way”, the web application will open a window with instructions to contact a health care provider or dial 911 if the person has intent or plan for self harm.

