**Schedule of Events**

**Study Schedule for Community Sample**

| **Study Period** | **I** |  | **II** |  |  |  | **III** |  |  |
| --- | --- | --- | --- | --- | --- | --- | --- | --- | --- |
| **Visit** | **1** | **2** | **3** | **4** | **5** | **6**  **SUM II** | **7** | **8** | **9**  **SUM III** |
| **Weeks Until Next Visit:** | **1** | **2** | **3** | **3** | **4** | **2** | **5** | **5** | **N/A** |
| **Interval Between Visits and**  **Target ( )** | **5-28 (7)** | **10-18 (14)** | **17-25 (21)** | **17-25 (21)** | **25-31 (28)** | **10-18 (14)** | **28-38 (35)** | **28-38 (35)** | **-** |
| Privacy Statement* | X |  |  |  |  |  |  |  |  |
| ASRS | X |  |  |  |  |  |  |  |  |
| Inclusion/exclusion criteria  (including PHQ-9) | X |  |  |  |  |  |  |  |  |
| Informed consent* | X |  |  |  |  |  |  |  |  |
| Demographics | X |  |  |  |  |  |  |  |  |
| Social Demographics | X |  |  |  |  |  |  |  |  |
| AAQOL-29 |  | X | X | X | X | X |  |  | X |
| CAARS-S:SV | X | X | X | X | X | X | X | X | X |
| PGI-I |  |  | X | X | X | X |  |  | X |
| Habits Timeline Followback (Alcohol, Nicotine, Caffeine, Marijuana, and Drugs) |  | X | X | X | X | X |  |  | X |
| Fagerstrom Test for Nicotine  Dependence |  | X |  | X |  | X |  |  | X |
| SASS |  | X |  | X |  | X |  |  |  |
| Driving Behavior Survey - Self  Report |  | X |  | X |  | X |  |  |  |
| Driving Behavior Survey - Other  Report |  | X |  | X |  | X |  |  |  |
| BRIEF-A |  | X |  | X |  | X |  |  |  |
| Epworth Sleepiness Scale |  | X | X | X | X | X |  |  | X |
| Beck Anxiety Inventory |  | X |  | X |  | X |  |  | X |
| Resource Utilization (use of medical or psych services or medication) | X | X | X | X | X | X | X | X | X |

* A privacy statement is obtained prior to patient completing the ASRS and an informed consent (ICD) is obtained prior to inclusion/exclusion questions via website. An additional online ICD is obtained prior to or at “Visit 1” if subject is eligible and opts in to proceed to the Community Sample.

Abbreviations: X = required at this visit; AAQOL-29 = Adult ADHD Quality of Life Scale 29-item;

BRIEF-A = Behavior Rating Inventory of Executive Function-Adult Version-Self; CAARS-S:SV = Conners’ Adult ADHD Rating Scale – Self Report: Screening Version; PGI-I = Patient Global Impression – Improvement; PHQ-9 = Patient Health Questionnaire; SASS = Social Adaptation Self- Evaluation Scale.

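### The Community Sample promises referral information when survey answers suggest self-harm risk, but the only trigger it names is scheduled at entry; showing the referral text at every later session would close the gap

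*Protocol*

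**What the plan says.** Protocol Attachment LYDZ(b).5 describes a non-interventional sample reporting over the web on the same visit schedule as the randomised trial. Participants "will interface only with a study website and will not be seen by an investigator or clinical trial site". Beyond the entry criteria there are no exclusions, and footnote 1 acknowledges that "this openness may result in the inclusion of patients with suicidal ideation".

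The footnote gives three responses to that risk:

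- A disclosure: "Consent forms will clearly indicate that no live or real-time review of forms will occur". The forms will also say that no care is provided.
- A general undertaking: "Care will be taken, however, to provide referral information in the event that structured survey responses" point to a raised risk of self-harm. It adds that participants will have no free-text fields.
- A worked example, attached to answers that "suggest increased risk of self-harm. For example, if a patient endorses the PHQ-9 item" on self-harm: in that case "the web application will open a window with instructions to contact a health care provider or dial 911" if there is intent or a plan.

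The Schedule of Events in the same attachment has no separate PHQ-9 row. The instrument appears only inside the inclusion/exclusion row ("including PHQ-9) | X"), which is marked at Visit 1 and nowhere else.

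**The concern.** The general undertaking has no time limit, but it works only if a later answer can meet its condition. The one answer named as meeting it belongs to an instrument that is not scheduled after the entry screen.

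Ideation can first appear, or return, after entry. A CS participant in that position has no clinician in the study, cannot write a free-text remark, and has been told that nobody reads the forms live. The referral window is then the only response to risk that the attachment describes, and the attachment describes no later point at which the participant would see it. What is at stake is the information participants receive. No comparison, estimate or power figure is involved.

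**Working it through.** This is mainly a reading of footnote 1 against the CS schedule, with one sum for the length of follow-up.

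**1. Where the named trigger sits.** The PHQ-9 is scheduled at 1 of the 9 CS visits (Visit 1), and at 0 of the 8 visits from Visit 2 to Visit 9.

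**2. What is collected afterwards.** The visits come from the CS schedule and the content from Sections 10.1 and 10.2 or the attachment itself.

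| Instrument | Visits from Visit 2 on | Content as described |
|---|---|---|
| AAQOL-29 | 2–6, 9 | four quality-of-life domains, including psychological health and life outlook |
| CAARS-S:SV | 2–9 | ADHD symptoms |
| PGI-I | 3–6, 9 | overall change |
| Habits Timeline Followback | 2–6, 9 | alcohol, nicotine, caffeine, marijuana, drugs |
| Fagerstrom test | 2, 4, 6, 9 | nicotine dependence |
| SASS | 2, 4, 6 | social adjustment |
| Driving survey, self | 2, 4, 6 | driving behaviour |
| Driving survey, other | 2, 4, 6 | driving behaviour, rated by an observer |
| BRIEF-A | 2, 4, 6 | executive function |
| Epworth scale | 2–6, 9 | daytime sleepiness |
| Beck Anxiety Inventory | 2, 4, 6, 9 | anxiety symptoms |
| Resource Utilization | 2–9 | use of services or medication |

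That makes 12 instruments, of which 0 are described as asking about self-harm. At Visits 7 and 8 only the CAARS-S:SV and Resource Utilization are collected.

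**3. How long this lasts.** The schedule's weeks-until-next-visit row gives, from Visit 2 to Visit 9, 2 + 3 + 3 + 4 + 2 + 5 + 5 = 24 weeks. The target days agree: 14 + 21 + 21 + 28 + 14 + 35 + 35 = 168 days, and 168 / 7 = 24. Across the visit windows:

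- shortest: 10 + 17 + 17 + 25 + 10 + 28 + 28 = 135 days (19.3 weeks)
- longest: 18 + 25 + 25 + 31 + 18 + 38 + 38 = 193 days (27.6 weeks)

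The stretch from Visit 6 to Visit 9 is 14 + 35 + 35 = 84 days at target (10 + 28 + 28 = 66 to 18 + 38 + 38 = 94).

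**4. What cannot be computed.** The documents give no rate of suicidal ideation, at entry or later, so no number of affected participants is offered.

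**The case against.** The strongest reply is that nothing here is wrong. The undertaking covers any structured answer and carries no visit limit. The PHQ-9 item is introduced only as an example, and which answers open a window is web-application detail that a protocol need not list. The count of 0 in 12 reflects short summaries, because item wordings are not printed; answers about emergency-room or psychiatric service use could serve as triggers. Consent pages are not in this copy and may carry standing crisis contacts. The authors also accepted these participants deliberately, because excluding them would defeat the aim of describing real-life complexity.

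Most of this stands, and it rules out three stronger readings that a reader might infer:

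- **That footnote and schedule contradict each other, or that the safeguard cannot work after entry.** Only the example is tied to Visit 1, so the documents do not show that no later trigger will be built.
- **That the CS should match the trial's checks.** In the trial, MADRS Item 10 is reviewed at Visits 4, 6 and 9 and can lead to the Columbia scale. Those patients receive study drug under clinical care, whereas the CS assigns no treatment. The contrast shows that the sponsor treats the risk as continuing, but it sets no standard for the CS.
- **That a known number of people is exposed.** Multiplying visits by enrolment would count web sessions, not harm.

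What the reply leaves standing is narrower. The sponsor undertook to provide referral information, and after Visit 1 the document describes no answer that would prompt it.

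**Conclusion.** The point holds as an inexpensive improvement to participant safety; it does not expose an error in the plan. As described, the referral undertaking has no evident trigger at any of the 8 visits after the entry screen, over 168 days at target (135 to 193). The conclusion rests on taking the protocol's summaries of the 12 later instruments as a fair account of their content. If one of them carries a self-harm item, or if the application already shows crisis contacts at login, the gap is smaller or absent, and footnote 1 need only say so. The analyses of the randomised trial and the CS are unaffected under either reading. The change should be made, with medium confidence, since undescribed triggers cannot be excluded.

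**What to change.** Show the referral instructions that the web application already holds (go to a health care provider, or call 911) at every CS session from Visit 2 to Visit 9, whatever the participant answers, and state this in footnote 1. A fixed display depends on no item and also reaches people who would not endorse one.

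The cost is minor web programming and one extra screen at 8 sessions that already take place online. No staff, visits, questionnaire items or analyses change. The documents do not cost the work; calling it cheap is a judgement based on the window already being planned. The downside is that participants see the same screen repeatedly and may come to ignore it. The documents offer no evidence on how much a standing notice helps.
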